## Abstract

**Introduction:**

Proactive and easily accessible interventions are needed to support people with long-term health conditions who experience limitations in activities of everyday life. However, there is a lack of interventions that promote self-management skills that prevent deterioration and improve health. The internet-based programme ‘Strategies for Empowering Activities in Everyday Life’ (SEE) supports people with long-term health conditions in developing self-management skills through knowledge, self-analysis and management strategies, promoting active and healthy daily life. This study protocol aims to evaluate the feasibility of SEE 2.0 and the study design.

**Methods and analysis:**

This feasibility study employs a pretest and post-test design with no control group, embedded within a mixed-method approach. The participants will include 30–40 clients, occupational therapists and managers involved in delivering SEE 2.0 in primary healthcare and hospital-based services. Data will be collected through assessments and forms at baseline, 4 months and 12 months after inclusion. Additionally, qualitative methods will be used to enhance the understanding of participants’ experiences.

**Ethics and dissemination:**

The study was approved by the Swedish Ethical Review Authority. The results will inform the refinement of SEE 2.0 and guide decisions on whether to proceed with planning a full-scale evaluation to assess the intervention’s effect. The results will be published in peer-reviewed scientific journals on websites and presented at conferences and seminars to reach various user groups.

**Trial registration number:**

NCT06484322.

STRENGTHS AND LIMITATIONS OF THIS STUDYThe intervention will leverage therapeutic mechanisms of the internet-based format to promote clients’ development of self-management in activities of everyday life.The combination of quantitative and qualitative data will provide a comprehensive assessment of the feasibility of the intervention and the study design.This study adopts a pragmatic approach, which, while challenging, will enhance the clinical applicability of the results.The small study sample without a control group will limit the ability to generalise potential effects.

## Introduction

 Establishing proactive interventions for people with chronic diseases and long-term disorders is a priority in Sweden and internationally and has the potential to use a person’s own resources to prevent deterioration and promote health.^1^,^3^ Many people may need early support to become proactive and develop self-management skills. For example, to promote a healthy balance of their engagement in various activities across different places and social contexts, aligned with what they want and need in their daily lives.^4^ Otherwise, and as a result of difficulties in managing their life situations, there is a risk that they will fall into a negative spiral of activity limitations and poor health.^4 5^ Thus, to prevent such limitations, it is crucial that healthcare provides early support to people with chronic diseases and long-term disorders across the different settings in which they receive care. This includes primary care as well as hospital-based outpatient and inpatient services. However, proactive interventions that support self-management are currently insufficient.^4^,^7^

Chronic disease encompasses long-term or lifelong health conditions that require constant attention and may also limit activities of everyday life.^8^ Long-term disorders are often of unclear origin and typically involve a combination of factors that affect everyday life, manifested primarily as symptoms of a behavioural nature.^9^ Some chronic diseases and long-term disorders have only a minimal impact and can often be effectively managed with medical and lifestyle-related measures. Others, such as rheumatological, neurological, cardiopulmonary, musculoskeletal and stress-related conditions, significantly affect people’s lives. The consequences of these long-term health conditions can be extensive, with reduced activity levels^10^,^12^ and varying degrees of difficulty in carrying out activities at home, in leisure time and at work.^11^,^15^ Living with altered activity levels can also affect sleep in many individuals.^16^ Unpredictable and fluctuating symptoms of long-term pain, stress and fatigue add to the complexity of everyday life and may necessitate extensive self-management.^617^,^19^ Fluctuations over days and longer periods pose challenges in developing effective management strategies.^17 18^ This may lead to difficulties in maintaining a healthy balance between different activities,^20^,^23^ which requires adapting the level and distribution of engagement when capacity varies.^18 24 25^ As a result, individuals across long-term health conditions often need to integrate a variety of management strategies to address these consequences in their everyday life.^612 17^,^19 26^

To meet these challenges, we have developed and initiated the evaluation of an internet-based occupational therapy intervention programme called ‘Strategies for Empowering activities in Everyday life’, SEE V.1.0.^427^,^31^ The programme supports people with long-term health conditions in developing self-management skills through knowledge, self-analysis and management strategies, promoting an active and healthy everyday life. SEE has three components: (1) an intervention programme including a web programme and materials for clients, (2) a web-based educational programme for the intervention providers—occupational therapists (OTs)—and (3) an intervention guide for OTs. Encouragingly, the results from previous studies of stroke clients in outpatient rehabilitation clinics^28 31^ indicate that SEE 1.0 facilitates self-management skills development and engagement in daily activities. Further, the OTs who delivered SEE demonstrated a transition towards an enhanced person-centred approach, facilitating the active role of clients during the intervention process.^29^ However, these studies^28 29 31^ revealed the continued need to evaluate the feasibility of the intervention programme across additional long-term health conditions and within a broader range of healthcare settings, following adjustments. Minor adjustments were needed to refine the intervention programme, therapist education programme and intervention guide. Furthermore, adjustments were needed to expand the target group, change the level of care/setting and revise recruitment procedures, introduce a new assessor-based outcome assessment and strengthen monitoring of adherence and implementation. After these changes were implemented, the first test of the updated version of SEE (V.2.0) was conducted in a case study.^32^ A feasibility study of SEE 2.0 in people with long-term health conditions within primary care and hospital-based services was then decided as the next step towards preparation for an evaluation trial. The present feasibility study is essential for identifying whether further adjustments of SEE 2.0 are needed and for assessing the research design for future large-scale studies. Moreover, even if an intervention proves to be feasible and effective, its adoption and integration can still be challenging. To overcome potential barriers to the integration of new interventions across healthcare settings, it is important to develop an understanding of relevant implementation aspects at an early stage.^33^,^35^

### Objectives

The project aims to evaluate the feasibility and implementation potential of SEE 2.0 for people with long-term health conditions across selected primary care and hospital-based services in Sweden. The following objectives were defined to assess SEE 2.0 and the study design:

Evaluate participant recruitment and retention.Evaluate the assessments’ suitability to detect outcomes of SEE at 4 and 12 months after entry into the programme, as well as the acceptability of the assessments.Evaluate client participants’ acceptability and value of SEE.Explore client participants’ experiences with the SEE intervention process and its influence on their self-management, everyday life and health.Evaluate participant (client and OT) adherence to SEE.Explore OTs’ and managers’ experiences of feasibility, acceptability, value and implementation potential of deliver SEE across different healthcare settings.

## Methods and analysis

### Design

This feasibility study of SEE 2.0 uses a pretest and post-test design with no control group, embedded within a mixed-method approach.^3336^,^40^ The data collection comprises outcome assessments, qualitative semistructured interviews, focus group (FG) discussions and study-specific forms for descriptive data. The study adheres to the Medical Research Council guidelines^33 41 42^ for evaluating complex interventions, and the feasibility study protocol follows the ‘Standard Protocol Items: Recommendations for Intervention Trials’.^43 44^ The trial is registered at ClinicalTrials.gov (ID: NCT06484322). A logical model^45^ provides a simplified overview of how SEE, including its components, is designed and expected to work (online supplemental table S1).

### Study setting

SEE 2.0 will be provided across multiple levels of care in northern Sweden: through primary healthcare services, including three healthcare centres, and within hospital-based outpatient and inpatient services. The internet-based intervention, SEE 2.0 will be delivered to clients through the ‘Support and Treatment Platform’, an e-health service available via the Swedish Healthcare Guide (1177.se), along with video meetings with the deliverer/OT.

### Eligibility criteria

#### Clients

People aged 18–75 years diagnosed with or at risk of developing chronic disease or long-term disorders (collectively referred to as long-term health conditions) receiving care in the involved healthcare settings will be considered for inclusion. Additionally, inclusion requires that the person is at risk of, or experiences activity limitations, expresses a need to develop self-management skills in everyday life and is motivated and ready to make changes in activities of daily living.^46^ This will be ascertained through a set of yes/no screening questions. To complete the programme, access and ability to use a screen/computer, internet and e-identification are also required. The exclusion criteria include conditions that significantly hinder the implementation of written and oral advice (eg, mental or cognitive illness), substance abuse and need for palliative care.

#### Professionals

The recruitment pool will consist of OTs, their managers and other staff in the healthcare settings who have volunteered to deliver SEE 2.0. No specific inclusion or exclusion criteria will be applied.

### Intervention

#### Intervention programme SEE 2.0 for clients

The goal of SEE 2.0 is to foster a well-distributed and balanced level of engagement in various daily activities across different contexts, including places and social interactions.^4 32^ To promote an active everyday life, the programme empowers clients with long-term health conditions to learn, self-analyse and change activities in everyday life. By gaining insights into their own patterns and balance in activities, clients can develop self-initiated management strategies to promote their health and well-being. By subsequently paying attention to these strategies, they can initiate and identify what works well and take an active role in preventing and overcoming challenges sustainably over time.

The internet-based SEE 2.0 intervention is person-centred and evolves through several phases, each comprising one or more modules.^4 32^ Throughout the entire intervention process, an OT continuously supports clients’ self-directed activities and change process related to each module by providing written feedback (asynchronous) and guided dialogues (synchronous), both delivered online. In the first web module in the intervention process, clients are supported in exploring their motivation and readiness to implement changes in their everyday activities. This is followed by an in-depth dialogue with an OT to further address these issues. Subsequently, clients engage in self-analysis by completing assessments of their activity engagement and use of management strategies. Their findings are further explored in one to two meetings in guided dialogues with the OT. Next, clients complete six web modules one at a time, each including concise educational videos accompanied by self-analyses and reflective tasks. Their work across the modules is supported by written feedback from the OT and by three guided in-depth dialogues with the OT, held at selected points during the process. The six modules aim to enhance self-management by imparting knowledge about strategies and modifications for everyday activities that can prevent disability and promote health. When clients have completed all modules and dialogues with the OTs, together, they create an activity plan for how to change their everyday life, including specific goals and activity-based management strategies to achieve an active everyday life (approximately 3–4 weeks into the programme). Clients receive ongoing support from the OT when the plan is implemented, using a person-centred approach that includes follow-up meetings tailored to their needs. The intervention process is expected to last between 2 and 4 months, but clients’ process of change can continue also when the intervention has come to an end. The OT also contacts and coordinates with other professionals if needed to implement the plan. The intervention process is complemented by written client materials introducing the intervention process as well as summarising and repeating important content from the web modules.

In addition to SEE 2.0, all clients receive usual care when needed. Usual care involves meeting with a physician for medical treatment, sick leave and/or referrals to other healthcare professionals, such as physiotherapists, medical social workers, psychologists and psychotherapists.

#### Educational programme for training SEE 2.0 interventionists

Before being eligible to deliver SEE 2.0, OTs complete a web-based educational programme and familiarise themselves with the intervention guide to ensure adherence to the intervention. During an online session, researchers introduce OTs to the self-paced educational format and encourage them to note any questions or topics for discussion in a follow-up meeting after the training. The educational programme includes videos that cover the evidence, theories and models underpinning the SEE programme. Additionally, there are practical videos demonstrating how to effectively deliver SEE to clients. An online session also guides OTs on how to assign clients to SEE on the National Healthcare Platform. In addition to the videos, OTs learn to navigate the intervention guide, which provides a step-by-step instruction for each module, emphasising person-centredness and the importance of active client engagement. After completing the training, OTs participate in a follow-up meeting with researchers to address any questions that they may have and repeat practical tips to prepare them to deliver SEE to clients. Throughout the study, OTs can reach out to researchers for supervision and support in implementing SEE as needed.

### Participant timeline

The study timeline is illustrated in the online supplemental table S2. The enrolment of the client participants began in September 2024 and is expected to be completed by December 2026. The person-centred intervention process is anticipated to vary between 2 and 4 months. Clients’ change processes and subsequent improvements are expected to continue even after the interventions end. Consequently, to identify potential long-term outcomes, evaluations will be conducted 4 months and 12 months after the start of SEE 2.0.

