### Recruitment

Potential clients can receive information in different ways from the involved healthcare settings. The healthcare staff can give a short oral briefing about the intervention programme and study during visits or telephone calls. Alternatively, information is provided via brochures and screens in the waiting rooms. Those who are interested in participation receive an information letter with complete details about the study. If they agree to participate, they send the informed consent (online supplemental material S3) to the researchers.

Once the researchers receive the consent form, potential participants are contacted by telephone. The content of the information letter is presented orally, and the potential participants are given the opportunity to ask questions to confirm their consent. They are then screened for the inclusion criteria, and if they meet the criteria, baseline assessments are initiated.

Personnel at the involved healthcare settings, including OTs, managers and other involved staff, receive oral and written information about the project before their written informed consent is sought. OTs and managers who are interested in being included in the study are asked if they would like to contribute, in addition to recruiting clients, by delivering SEE. Thus, SEE 2.0 will be delivered by OTs who want to deliver the new intervention and complete the educational programme.

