### Data collection

An overview of the timeline of the various methods used to collect data from clients, OTs, managers and other staff is presented in online supplemental table S2. Outcome assessments will be conducted at baseline and at 4 and 12 months postintervention. Additionally, at 4 months, clients will rate the acceptability and value of SEE 2.0. Intervention adherence will be evaluated by forms and field notes throughout the intervention. Qualitative experiences of the programme will be gathered through semistructured interviews with clients and FG discussions with staff.

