### Data analysis

The statistical analysis will assess the suitability of the assessments in detecting outcomes of SEE 2.0 at 4 and 12 months after entry into the programme. In this study, descriptive statistics and non-parametric tests will be used to identify patterns of changes and compare outcomes on respective outcome assessments over time, from baseline to 4 and 12 months. The intention-to-treat approach will be applied, and per-protocol analyses will be conducted if necessary. A gender perspective will be considered in the data analysis to identify potential differences and similarities in outcomes. Sociodemographic characteristics in relation to outcomes will be analysed descriptively. The significance level will be set at p<0.05 for all the statistical tests. All the data from the enrolment process, the number of complete or incomplete assessments, study-specific forms for adherence, acceptability, value, potential harms and field notes will be compiled descriptively^38 66^ by analysis of content and descriptive statistics. The qualitative interviews with the clients will be analysed using the constant comparative method of grounded theory,^61^ as this method is suitable for identifying patterns in interactions, strategies and processes such as intervention processes. The FG discussions will be analysed with FG analysis^63 64^ to identify themes in the collective experiences.

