## Ethics and dissemination

The project has been approved by the Swedish Ethical Review Authority (EPM Dnr: 2023-08032-01, 2024-042277-02, 2025-00635-02, 2025-04193-02) and will be conducted in accordance with the Declaration of Helsinki,^67^ the Swedish law of ethical research on humans^68^ and the GDPR.^65^ All participants will receive information about what participation in the research means both orally and in writing and can ask questions before they sign the written informed consent form and send it to the researchers. This includes information about the potential benefits or risks of participation and the right to withdraw their participation in the study at any time without explanation. They will also be informed that the data will be treated as confidential. Given the small sample size from a local perspective, the amount of personal information will be limited to ensure that participants’ identities cannot be derived from study presentations as in scientific papers.

During the implementation of the internet-based intervention SEE 2.0, patient safety and the protection of sensitive data are ensured by using the support and treatment platform on Sweden’s 1177 National Healthcare Guide. Logging in to the platform is performed via national e-identification. Based on person-centredness, clients can choose whether to carry out the guiding dialogues that support their change process digitally or via personal meetings at the healthcare settings. For digital meetings, secure forums recommended by the organisation will be used. The researchers will not have access to 1177 or medical records.

The results will be presented at conferences that attract researchers, professionals and the general public. Particular emphasis will be placed on reaching out to interest groups (such as patient and professional associations). The studies will be published in international scientific journals, and the researchers will adhere to established authorship guidelines. Popular science summaries of the results will also be created for various audiences and shared on the LTU website and social media.

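### The 4- and 12-month assessments have four different time origins, and at least two of them leave an included client who never starts SEE 2.0 with no assessment due

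*Protocol article*

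**What the plan says.** The protocol article dates the follow-up assessments in five places, using four different origins.

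- **Inclusion** (Abstract, Methods and analysis): "Data will be collected through assessments and forms at baseline, 4 months and 12 months after inclusion".
- **Entry into the programme** (Objectives): "at 4 and 12 months after entry into the programme, as well as the acceptability of the assessments". Data analysis repeats this: "detecting outcomes of SEE 2.0 at 4 and 12 months after entry into the programme".
- **Start of SEE 2.0** (Participant timeline): "evaluations will be conducted 4 months and 12 months after the start of SEE 2.0".
- **End of the intervention** (Data collection): "Outcome assessments will be conducted at baseline and at 4 and 12 months postintervention".

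On the order of events, Recruitment places consent first, then a telephone call and screening: "They are then screened for the inclusion criteria, and if they meet the criteria, baseline assessments are initiated". The section on suitability and acceptability of outcome assessments adds that self-report forms go out by post and that the video interview for the SDO is arranged once they are returned. Starting SEE 2.0 is not a step in either description.

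On analysis, the article states: "The intention-to-treat approach will be applied, and per-protocol analyses will be conducted if necessary". Enrolment and retention says that enrolment, inclusion, retention and drop-out rates will all be measured, without giving a denominator.

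**The concern.** A client can consent, pass screening, complete the baseline and then never begin the programme. If follow-up is dated from the start of SEE 2.0 or from its end, the 4- and 12-month dates do not exist for that client. No questionnaire pack falls due and no SDO interview is arranged.

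An intention-to-treat approach in a single-arm study can only mean analysing all included clients, whatever they received. A schedule that makes follow-up depend on receiving the intervention works against it. Reconciling every passage to the start of SEE 2.0 would remove the contradiction and still leave this gap.

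Two objectives are at stake: recruitment and retention, and the suitability of the assessments to detect outcomes at 4 and 12 months. The forms on acceptability, value and potential harm travel in the 4-month pack, so a never-starter would not receive those either. The Discussion itself acknowledges that digital delivery may not suit all clients, and the Abstract says the results will guide whether to plan a full-scale evaluation. Clients who sign up but do not begin are informative for that decision.

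**Working it through.** The article gives no retention target, drop-out rate or never-start rate, so there is no planned figure to reproduce. The check has two parts.

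**1. The time origins side by side**

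The intervention is expected to last 2 to 4 months (Intervention; Participant timeline). Measured from the start of SEE 2.0, an assessment set at 4 or 12 months after the end of the intervention falls at:

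- 4 + 2 = 6 to 4 + 4 = 8 months;
- 12 + 2 = 14 to 12 + 4 = 16 months.

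The Participant timeline puts the same assessments at 4 and 12 months from the start. Data collection therefore differs from it by 2 to 4 months at each time point.

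| Origin | Section | Does a never-starter have a date? |
|---|---|---|
| Inclusion | Abstract | Yes |
| Entry into the programme | Objectives; Data analysis | Only if entry does not mean starting SEE |
| Start of SEE 2.0 | Participant timeline | No |
| End of the intervention | Data collection | No |

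Only the inclusion origin clearly covers every included client.

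**2. Possible effect on retention (illustration only)**

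Let *r* be retention among starters and *s* the share of included clients who never start and are not assessed. Retention over all included clients is *r*(1 − *s*). If retention were instead counted among starters, it would be too high by *r* × *s*.

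Inputs: 30–40 clients (Sample size). *r* = 85% and *s* = 0–20% are assumptions; neither is in the article. A never-start share of 5–20% corresponds to 30 × 0.05 = 1.5 up to 40 × 0.20 = 8 clients.

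- *s* = 0%: 0.85 × 1.00 = 85%; difference 0.
- *s* = 5%: 0.85 × 0.95 = 81%; difference about 4 points.
- *s* = 10%: 0.85 × 0.90 = 76.5%; difference 8.5 points.
- *s* = 20%: 0.85 × 0.80 = 68%; difference 17 points.

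Whole-client example, also assumed: 35 included, 4 never start, 27 assessed at 12 months. Among starters this is 27/31 = 87% (Wilson 95% CI 71–95%). Among all included it is 27/35 = 77% (61–88%). The intervals overlap widely because both are the same 27 clients over different denominators. The gap is one of definition, not of sampling error.

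**The case against.** The strongest reply is that the start of SEE 2.0 is not the settled rule. The Abstract says inclusion, and under that origin never-starters have both assessments due. This is right, and it is why the firm defect is the contradiction between sections. It does not remove the problem, because the two sections that describe the schedule and the data collection use origins that fail for these clients.

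A reader might go further and infer any of the following. The article does not support them.

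- *Never-starters are dropped from the intention-to-treat set.* No section says so. An undefined visit date leaves an outcome missing; it does not by itself remove the client from the set.
- *Retention will be overstated.* This needs a starters-only denominator, which the article does not state. Since inclusion and drop-out are both measured, never-starters could be counted as drop-outs among those included.
- *The researchers cannot know who has not started.* Ethics and dissemination does say "The researchers will not have access to 1177 or medical records", so they cannot see it on the platform. But Intervention adherence provides for continuous field notes from meetings with clients and occupational therapists, and there are recurring discussions with the therapists. Non-starting could be reported by those routes, although the structured adherence interviews, timed at completion of phase 4 and of the intervention, would not be triggered.
- *Assignment on the platform is the start.* The educational programme section says only that therapists are shown how to assign clients; the article does not define the start.

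It is also fair to say that the definition of the analysis set and the retention denominator may sit in a fuller protocol or analysis plan, and that their absence here is no fault. The conflicting timing statements are different, because they are in this document. Finally, inclusion requires motivation, readiness and digital access, so few clients may fail to start.

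**Conclusion.** The point stands in this form. The article dates the 4- and 12-month assessments from four origins that cannot all apply. Under two of them, and a third if entry means starting, an included client who never starts has no assessment due. That client's follow-up outcomes are missing by design, which does not fit the stated intention-to-treat approach.

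The effect on retention is a possibility, not a demonstrated bias. It arises only if retention is counted among clients due for follow-up, and its size rests wholly on an assumed never-start rate: none if all start, about 4 to 17 points at 5–20% never starting with 85% retention among starters. The study is small, single-arm and descriptive on retention, so this is a correction worth making rather than a threat to the study as a whole. It changes which data are collected, so it cannot be fully repaired at analysis.

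**What to change.** 1. Reconcile the Abstract, Objectives, Participant timeline, Data collection and Data analysis to one time origin that exists for every included client, such as the inclusion or baseline date. If the start of SEE 2.0 is kept for starters so that time since exposure is comparable, state that clients with no reported start are followed from the inclusion or baseline date, which the researchers hold.
2. State in Participant timeline that every client with a baseline receives the 4- and 12-month assessments.
3. State in Data analysis that the intention-to-treat analysis covers all included clients, whether or not SEE 2.0 was started.
4. Report retention over all included clients, with never started as its own line.

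The cost is a few sentences, a calendar rule for sending packs, and a few extra postal packs and interviews. The reported retention may be less favourable, and a few clients will be assessed who received no SEE 2.0. If all clients are anchored on inclusion, time since starting will vary between clients at each assessment, so the start date should be recorded where there is one.
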